## 5.2 Vaccine Storage

MSP2-C1/ ISA720 vaccine and ISA720 control should be maintained at 2 - 8oC until just prior to administration. Vaccine/ Control should NOT be frozen at any time. Single-dose vials should be stored in the upright position.

## 5.3 Vaccine Preparation

Vaccine/ Control will be prepared by the site pharmacist/ nominee for each participant according to the Master Randomisation Schedule. The Vaccine/ Control vial should be maintained at 2-8ºC until just prior to vaccination. The required vial will be removed from the refrigerated storage, gently inverted several times to warm the contents and then drawn up into a syringe. The site pharmacist/ nominee will apply a Participant specific label to the syringe confirming the Protocol Number, Participant Identification Number, Initials and vaccination date.

## 5.4 Vaccine Accountability

The site pharmacist/ nominee is responsible for maintaining an accurate inventory and accountability record of vaccine/ control supplies for this study. Partially used vials may not be administered to other volunteers.

## 5.5 Disposition of Used/Unused Supplies

After administration of vaccine/ control dose, the used vials will be stored in the study pharmacy at the study site, and will be accounted for and stored until monitoring by the study sponsor. Used vials may be disposed of according to study site protocol after monitoring has been completed. Final disposition of unused vaccine supplies will be determined by the Sponsor in conjunction with the trial site pharmacy.

# 6.0 Study Procedures

The following sections provide a detailed listing of the procedures and studies to be performed in this protocol at designated time points. Each volunteer will receive 3 immunisations at 12 week intervals and will be asked to return to the clinic for 16 visits. The total volume of blood is approximately **450** mL to be drawn over the duration of the trial (approximately 1 year). This is approximately the same volume collected when donating a single unit of blood and should not compromise the health of trial participants over this extended period.

## 6.1 Recruitment and Enrollment

Volunteers will respond to HREC-IRB approved advertisements distributed by the clinical trial site in local newspapers and posted flyers. A screening visit will be scheduled after an initial contact screen by clinical trial staff consisting of background information of the trial. During this initial screening visit, the volunteer will read the consent form and be encouraged to ask questions. Volunteer willing to be considered for participation may sign the screening consent form during the screening visit, or return after further consideration. The volunteer will be given a copy of the consent for their records. Rolling recruitment and enrollment will occur to fill the first dose cohort followed by the second dose cohort. After enrollment into a dose group, volunteers will be randomly assigned to receive either the MSP2-C1/ ISA720 vaccine or ISA720 Control.

On any given day of first vaccination, more volunteers (up to three) may be invited to participate than are scheduled to be vaccinated that day. If not vaccinated, these alternates will be invited to return on the next day of first vaccination. Alternates will be compensated for the study visit even if not vaccinated, as described in the participation information and consent form and Section 10.7.

## 6.2 Screening (Up to 28 Days Prior to Vaccination)

1. Explain the study via the Participation Informed Consent (Appendix 6) and gain Screening Informed Consent (Appendix 5) from the volunteer.
2. Ensure the subject has signed the Screening Informed Consent and received a signed copy.
3. Elicit a complete medical history, including menstrual and contraceptive history and/or history of surgical sterility for female participants. Counsel females of childbearing potential to utilize effective contraception during the study.
4. Elicit a social history including smoking and alcohol use
5. Undertake a complete physical examination.
6. Counsel females of childbearing potential to utilize effective contraception during the study.
7. Obtain approximately 19 mL of blood for hematology, biochemistry, serologic tests for viral hepatitis B and C and HIV in all volunteers and an extra 10 mL blood for -HCG testing in females. Pre- and post-test counseling for blood borne viruses will take place as per existing SOP.
8. Obtain 45 ml blood for PBMC for CMI and serum for CMI assay for CMI immunity testing and for humoral immunity studies (anti-MSP2) by GIA and IFA. NB Sample can be collected Study Day 0 Pre-vaccination depending on laboratory availability.
9. Urine collection for dipstick testing.
10. Verify inclusion/exclusion criteria.
11. A screening number will be assigned to each volunteer.

## 6.3 Immunisation Procedure

Eligible participants will receive three immunisations 12 weeks apart. Vaccine/ Control will be prepared by the site pharmacist (or designee) according to Section 5.3 and provided to the vaccinator for administration within 30 minutes of being drawn into the syringe. A dose of 0.5 mL of the vaccine will be delivered by IM injection in the deltoid muscle of the arm after preparation of the site with alcohol. Successive vaccinations will be given in alternating arms.

## 6.4 Clinical Monitoring and Evaluation

The following sections provide a detailed listing of the procedures and studies to be performed in this protocol at designated time points. See **Appendix 1** for a tabular representation of study procedures. In addition to the procedures listed below, photographs of the injection site may be taken at baseline and/or on follow-up visits to better assess local reactogenicity.

Study Day 0 **(FIRST VACCINATION, visit 1)**

1. Verify that all applicable eligibility criteria have been met.
2. For females, obtain a urine sample for -hCG testing. Ensure that test is negative before vaccinating; a positive test will exclude the volunteer from the trial.
3. Verify that Study Participation Informed Consent was obtained and a copy of this provided to the subject.
4. Medical Investigator to perform medical history and physical examination, to assess eligibility to enter vaccine phase.
5. Record vital signs (blood pressure, temperature, heart rate, and respiratory rate).
6. Obtain approximately 24 mL of blood for hematology (FBC and differential), biochemistry (electrolytes creatinine, liver function tests, CPK), and blood for study of humoral immune response by anti-MSP2 ELISA.
7. Administer the vaccine, and record which arm utilised.
8. Observe for at least 30 minutes after vaccination to evaluate for immediate adverse reactions. Vital signs will be repeated prior to leaving the clinic.
9. Education by study staff during 30-minute post-immunisation wait period describing proper use of digital thermometers, injection-site reaction measurement, and vaccine side-effect diaries. Study staff will also discuss signs and symptoms of potential AEs.
10. Distribute Days 0-6 diary card.
11. Record adverse events and concomitant medications.

Study Day 1 (Phone Call ONLY)

1. Phone call to inquire about diary card entries and injection site reactions since last visit.

Study Day 3 (visit 2)

1. Study staff to perform targeted history and examine injection site, emphasising examination of any acute complaints, with review by the medical investigator if required.
2. Record vital signs.
3. Obtain approximately 9 mL of blood for haematology (FBC and differential), and biochemistry (creatinine, liver function tests).
4. Record adverse events and concomitant medications.

Study Day 7 +/- 1 (visit 3)

1. Medical Investigator to perform medical history and physical examination including examination of injection site, emphasising examination of any acute complaints, to assess continued eligibility.
2. Record vital signs.
3. Collect Days 0-6 diary card and review completion. Refer any complaints to Medical Investigator for assessment.
4. Distribute Days 7-13 diary card.
5. Record adverse events and concomitant medications.

Study Day 14 +/- 2 (visit 4)

1. Medical Investigator to perform medical history and physical examination including examination of injection site, emphasising examination of any acute complaints and targetted history taking to elicit symptoms of muscle damage (myositis), as well as exercise history, emphasizing changes in pattern of regular exercise.
2. Record vital signs.
3. Collect Days 7-13 diary card and review completion. Refer any complaints to Medical Investigator for assessment.
4. Distribute Days 14-27 diary card.
5. Obtain approximately 14 mL of blood for haematology (FBC and differential), and biochemistry (creatinine, liver function tests, CPK).
6. Record adverse events and concomitant medications.

Study Day 21 +/- 3 (Phone call ONLY)

1. Phone call to inquire about diary card entries and injection site reactions since last visit.

Study Day 28 +/- 5 (1 month after FIRST vaccination, visit 5)

1. Study staff to perform targeted history and examine injection site, emphasising examination of any acute complaints, with review by the medical investigator if required.
2. Record vital signs.
3. Collect Days 14-27 diary card and review completion. Refer any complaints to Medical Investigator for assessment.
4. Obtain 55 ml of blood for collection of blood for humoral immunity studies by anti-MSP2 ELISA, and PBMC and serum for study of cell mediated immunity.
5. Record adverse events and concomitant medications.

Study Day 56 +/- 7 (2 months after FIRST vaccination, visit 6)

1. Medical Investigator to perform medical history and physical examination including examination of injection site, emphasising examination of any acute complaints, to assess continued eligibility.
2. Record vital signs.
3. Obtain approximately 9 mL of blood for haematology (FBC and differential), and biochemistry (creatinine, liver function tests).
4. Record adverse events and concomitant medications.

Study Day 84 +/- 7 (**SECOND vaccination, visit 7)**

1. Medical Investigator to perform medical history and physical examination, to assess continued eligibility to enter treatment phase.
2. For females, obtain a urine sample for -hCG testing. Ensure that test is negative before vaccinating; a positive test will exclude the volunteer from the trial.
3. Record vital signs.
4. Obtain approximately 24 mL of blood for haematology, (FBC and differential), biochemistry (creatinine, liver function tests CPK) and approximately 55 mL blood for humoral immunity studies by anti-MSP2 ELISA.
5. Administer the vaccine in the alternate arm and record the arm utilised.
6. Observe for at least 30 minutes after vaccination to evaluate for immediate adverse reactions. Vital signs will be repeated prior to leaving the clinic.
7. Education by study staff during 30-minute post-immunisation wait period describing proper use of digital thermometers, injection-site reaction measurement tools and patient diaries. Study staff will also discuss signs and symptoms of potential AEs.
8. Distribute Days 0-6 diary card.
9. Record adverse events and concomitant medications.

Study Day 85 (1 day after SECOND vaccination, phone call ONLY)

1. Phone call to inquire about diary card entries and injection site reactions since last visit.

Study Day 87 (3 days after SECOND vaccination, visit 8)

1. Study staff to perform targeted history and examine injection site, emphasising examination of any acute complaints, with review by the medical investigator if required.
2. Record vital signs.
3. Obtain approximately 9 mL of blood for haematology (FBC and differential), and biochemistry (creatinine, liver function tests).
4. Record adverse events and concomitant medications.

Study Day 91 +/- 1 (7 days after SECOND vaccination, visit 9)

1. Medical Investigator to perform medical history and physical examination including examination of injection site, emphasising examination of any acute complaints, to assess continued eligibility.
2. Record vital signs.
3. Collect Days 0-6 diary card and review completion. Refer any complaints to Medical Investigator for assessment.
4. Distribute Days 7-13 diary card.
5. Record adverse events and concomitant medications.

Study Day 98 +/- 2 (14 days after SECOND vaccination, visit 10)

1. Medical Investigator to perform medical history and physical examination including examination of injection site, emphasising examination of any acute complaints and targetted history taking to elicit symptoms of muscle damage (myositis), as well as exercise history, emphasizing changes in pattern of regular exercise.

2. Record vital signs.

3. Obtain approximately 14 mL of blood for haematology (FBC and differential), and biochemistry (creatinine, liver function tests, CPK).

4. Collect Days 7-13 diary card and review completion. Refer any complaints to Medical Investigator for assessment.

5. Distribute Days 14-27 diary card.

6. Record adverse events and concomitant medications.

Study Day 105 +/- 3 (Phone call ONLY)
1. Phone call to inquire about diary card entries and injection site reactions since last visit.

Study Day 112 +/- 5 (28 days after SECOND vaccination, visit 11)

1. Study staff to perform targeted history and examine injection site, emphasising examination of any acute complaints, with review by the medical investigator if required.
2. Record vital signs.
3. Collect Days 14-27 diary card and review completion. Refer any complaints to Medical Investigator for assessment.
4. Obtain 55 ml of blood for collection of blood for humoral immunity studies by anti-MSP2 ELISA, GIA and IFA, and PBMC and serum for study of cell mediated immunity.
5. Record adverse events and concomitant medications.

Study Day 140 +/- 7 (56 days after SECOND vaccination, visit 12)

1. Medical Investigator to perform medical history and physical examination including examination of injection site, emphasising examination of any acute complaints, to assess continued eligibility.

2. Record vital signs.

3. Obtain approximately 9 mL of blood for haematology (FBC and differential), and biochemistry (creatinine, liver function tests).

4. Record adverse events and concomitant medications.

Study Day 168 +/- 7 (**THIRD VACCINATION, visit 13**)

1. Medical Investigator to perform medical history and physical examination, to assess continued
eligibility to enter treatment phase.

2. Obtain approximately 24 mL of blood for haematology, (FBC and differential), biochemistry (creatinine, liver function tests CPK), and humoral immunity studies by anti-MSP2 ELISA.

3. For females, obtain a urine sample for -hCG testing. Ensure that test is negative before vaccinating; a positive test will exclude the volunteer from the trial.

4. Record vital signs.

5. Administer the vaccine in the alternate arm.

6. Observe for at least 30 minutes after vaccination to evaluate for immediate adverse reactions. Vital signs will be repeated prior to leaving the clinic.

7. Education by study staff during 30-minute post-immunisation wait period describing proper use of digital thermometers, injection-site reaction measurement tools, and patient diaries.  Study staff will also discuss signs and symptoms of potential AEs.

8. Distribute Days 0-6 diary card.

9. Record adverse events and concomitant medications

Study Day 169 (1 day after THIRD vaccination, Phone call ONLY)

1. Phone call to inquire about diary card entries and injection site reactions since last visit.
 
Study Day 171 (3 days after THIRD vaccination, visit 14)

1. Study staff to perform targeted history and examine injection site, emphasising examination of
any acute complaints, with review by the medical investigator if required.

2. Record vital signs.

3. Obtain approximately 9 mL of blood for haematology (FBC and differential), and biochemistry (creatinine, liver function tests).

4. Record adverse events and concomitant medications.

Study Day 175 +/- 1 (7 days after THIRD vaccination, visit 15)

Medical Investigator to perform medical history and physical examination including examination of injection site, emphasising examination of any acute complaints, to assess continued eligibility.

Record vital signs.

Collect Days 0-6 diary card and review completion. Refer any complaints to Medical Investigator for assessment.

Distribute Days 7-13 diary card.

Record adverse events and concomitant medications.

Study Day 182 +/- 2 (14 days after THIRD vaccination, visit 16)

1. Medical Investigator to perform medical history and physical examination including examination of injection site, emphasising examination of any acute complaints and targetted history taking to elicit symptoms of muscle damage (myositis), as well as exercise history, emphasizing changes in pattern of regular exercise.
2. Record vital signs.
3. Collect Days 7-13 diary card and review completion. Refer any complaints to Medical Investigator for assessment.
4. Distribute Days 14-27 diary card.
5. Obtain approximately 14 mL of blood for haematology (FBC and differential), and biochemistry (creatinine, liver function tests, CPK).
6. Record adverse events and concomitant medications.

Study Day 189 +/- 3 (Phone call ONLY)
1. Phone call to inquire about diary card entries and injection site reactions since last visit.

Study Day 196 +/- 5 (28 days after third vaccination, visit 17)

- 1. Study staff to perform targeted history and examine injection site, emphasising examination of any acute complaints, with review by the medical investigator if required.
  2. Record vital signs.
  3. Collect Days 14-27 diary card and review completion. Refer any complaints to Medical Investigator for assessment.
  4. Obtain 55 ml of blood for collection of blood for humoral immunity studies by anti-MSP2 ELISA, GIA and IFA, and PBMC and serum for study of cell mediated immunity.

5. Record adverse events and concomitant medications.

Study Day 336 +/- 14 (6 months after THIRD vaccination, visit 18)

1. Medical Investigator to perform medical history and physical examination including examination of injection site, emphasising examination of any acute complaints.
2. Record vital signs.
3. Obtain 55 ml of blood for collection of blood for humoral immunity studies by anti MSP2 ELISA, GIA and IFA, and PBMC and serum for study of cell mediated immunity.

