## 4.4 Contraindications to Vaccination

The following criteria should be checked prior to each immunisation and are contraindications to further immunisation. However, the participant will be encouraged to remain in the safety evaluation for doses already received.

1. Hypersensitivity reaction following administration of the study vaccine.
2. Pregnancy, as determined by a positive urine β-hCG.
3. Occurrence of severe chronic disease (such as diabetes or tuberculosis), which in the view of the investigators could jeopardize the safety of study participant or interpretation of the safety or immunogenicity data.

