## 4.6 Subject Withdrawal Criteria

A volunteer will not be considered to have completed the trial if any of the circumstances outlined below apply. However, any volunteer who has received at least one dose of vaccine will be encouraged to remain in the safety evaluation for the duration of the study.

1. *Research terminated by sponsor, investigator, or regulatory body* – applies if the study is terminated by a sponsor, investigator, or regulatory body for any reason.
2. *Withdrawal of consent* – applies to a participant who withdraws consent to participate in the study for any reason.
3. *Noncompliant with protocol* – applies to a participant who does not comply with protocol-specific visits or evaluations, on a consistent basis, such that adequate follow-up is not possible and the participant’s safety would be compromised by continuing in the trial.
4. *Significant adverse event* - applies to a participant who is withdrawn from the study by the investigator due to an adverse event, serious or otherwise.
5. *Lost to follow-up* - applies to a participant who consistently does not return for protocol study visits, or who cannot be contacted or located.
6. If *new safety data* becomes available during the trial that impacts participant health.
7. *Pregnancy*. Should a female volunteer become pregnant during the course of the study, she will be withdrawn from the study and followed for the duration of the pregnancy. The outcome of the pregnancy will be documented.
8. If, in the judgment of the investigator, the subject has a condition that would interfere with safety or compliance with follow-up visits.
9. *Other* – is a category used when previous categories do not apply, and requires an explanation.

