### 6.4.1 Clinical Monitoring and Evaluation of Subjects Withdrawn from Vaccinations

Participants may be withdrawn from further vaccinations as described in Sections 4.4, 4.5 and 4.6 above. Participants who have received at least one vaccination will be encouraged to continue in the study for safety follow-up according to a modified visit schedule.

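### The Day 84 and Day 168 visit lists exclude a volunteer with a positive pregnancy test from the trial after one or two doses, while sections 4.4, 4.6, 6.4.1 and Appendix 1 keep a dosed volunteer in safety follow-up

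*Protocol*

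**What the plan says.** All references are to the protocol.

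- **Section 6.4, Study Days 0, 84 and 168.** The instruction on the urine pregnancy test is worded identically at all three vaccination visits: "Ensure that test is negative before vaccinating; a positive test will exclude the volunteer from the trial". The Day 84 and Day 168 entries do not refer to any other section.
- **Section 4.4.** One of the listed contraindications to further immunisation is "Pregnancy, as determined by a positive urine β-hCG". The paragraph above the list adds: "However, the participant will be encouraged to remain in the safety evaluation for doses already received".
- **Section 4.6.** The opening encourages everyone with one or more doses to stay in safety follow-up until the study ends. Item 7, on pregnancy, says that "she will be withdrawn from the study and followed for the duration of the pregnancy", and that the pregnancy outcome will be documented.
- **Section 6.4.1.** For those withdrawn from vaccination under 4.4, 4.5 or 4.6: "Participants who have received at least one vaccination will be encouraged to continue in the study for safety follow-up". Sections 6.4.1.1 and 6.4.1.2 set out the modified visits.
- **Appendix 1.** Footnote 7 waives vaccination and the pregnancy test at Days 84 and 168 for a participant withdrawn from vaccination. Footnote 6, which waives a whole visit, is not attached to Days 84, 168 or 336, so those visits stand.
- **Section 4.2.** The lead-in allows exclusion not only at screening but also on vaccination days and between blood samples. Item 16 is pregnancy.

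**The concern.** A sentence suited to an undosed volunteer has been carried over to two visits at which she has already been exposed. For the same event, a positive urine test after dosing, some passages put her out of the trial and others keep her in safety follow-up. A site cannot do both, and the visit list gives no pointer to the section meant to govern.

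Safety and tolerability are the primary objective. Section 9.1.2 tabulates adverse events after each vaccination and over the whole study. Each dose group has 12 vaccinees, and section 3.3 allows no replacement after the first vaccination. Section 10.3 describes the risk to the foetus as unknown, and section 7.1.2 makes a congenital anomaly a serious adverse event. Follow-up of a pregnancy exposed to the vaccine is therefore information this trial would want, and it cannot be recovered later if contact is ended.

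**Working it through.** The protocol gives no figure for this event, so there is no stated figure to reproduce. The check compares the passages and then works out how much follow-up is at stake.

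**1. What each place prescribes for a dosed volunteer with a positive test**

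| Place | Further vaccination | Status and follow-up |
| --- | --- | --- |
| 6.4, Days 84 and 168 | No | Excluded from the trial; no follow-up mentioned |
| 4.2 lead-in with item 16 | Not addressed | May be excluded, including on a vaccination day |
| 4.4 | No | Encouraged to stay in the safety evaluation |
| 4.6 opening | Not addressed | Not a completer; encouraged to stay in the safety evaluation to the end of the study |
| 4.6 item 7 | Not addressed | Withdrawn from the study; pregnancy followed and outcome documented |
| 6.4.1 | Already withdrawn from vaccination | Encouraged to continue on a modified schedule |
| Appendix 1 | Waived | Day 84, 168 and 336 visits retained |

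Sections 4.4, 4.6 (opening), 6.4.1 and Appendix 1 are compatible with one another. The 6.4 lists are not compatible with them. Section 4.2, and the withdrawal wording of 4.6 item 7, lean towards the 6.4 lists.

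**2. Does section 6.4.1 resolve the conflict?** Only in part. It covers withdrawals under 4.4, 4.5 and 4.6. It does not mention exclusion under 4.2 or under the 6.4 visit lists. A site that records the volunteer as excluded at Day 84 is not sent to the modified schedule.

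**3. Follow-up at stake under the literal reading (nominal days)**

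- Positive at Day 84: 336 − 84 = 252 days. The modified visits after that day are Days 168 and 336.
- Positive at Day 168: 336 − 168 = 168 days. The modified visit after that day is Day 336.

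**4. Order of steps within the visit.** At Day 84 the pregnancy test is step 2; at Day 168 it is step 3. At both visits adverse events are recorded at step 9. The preceding visits are Days 56 and 140, so the interval that could go unrecorded is 84 − 56 = 28 days or 168 − 140 = 28 days.

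**5. How often it might happen (assumptions, not protocol figures).** The protocol gives neither the number of women nor a pregnancy rate. Assume 15 of the 30 volunteers are women and the pregnancy rate under contraception is 1% to 5% a year, over the 24 weeks from first to third dose:

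- 15 × 24/52 × 0.01 = 0.07
- 15 × 24/52 × 0.05 = 0.35

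The result scales directly with both assumptions. On these values, fewer than one pregnancy is expected.

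**The case against.** The strongest reply is that the protocol, read as a whole, already has a workable rule and the visit lists are merely loose. Sections 4.4, 4.6 and 6.4.1 can be read together: no further dose, safety follow-up encouraged, pregnancy outcome documented. Section 6.4.1 sits directly after the visit lists, and Appendix 1, which 6.4 names as its tabular form, agrees with it. Staff have all of these to hand, so a careful site would lose nothing. This stands as a limit on the likely harm. It does not remove the contradiction, because the visit instruction and section 4.2 say otherwise and neither gives way to the other sections.

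A reader might infer more than the text supports:

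- **That her data are dropped from the safety analysis.** No passage deletes data already collected, and section 9.1.2 defines no population that omits her. What is at risk is follow-up from that visit on, plus unrecorded events since the previous visit.
- **That section 4.6 limits follow-up to the pregnancy.** Item 7 does not say so, and the opening of 4.6 encourages safety follow-up for any dosed volunteer.
- **That the visit lists are the only place that excludes her.** Section 4.2 does so too.
- **That each case costs 1/12 = 8.3% of a dose group.** This treats her as contributing nothing, although her data up to that visit remain. She may also be one of the 6 control recipients among the 30.

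Finally, continued follow-up is encouraged in these sections, not required. Even a reconciled text would not guarantee that it is obtained.

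**Conclusion.** The contradiction is established from the text alone: the Day 84 and Day 168 lists in 6.4, supported by the 4.2 lead-in, conflict with 4.4, the opening of 4.6, 6.4.1 and Appendix 1. It is an inconsistency of wording, with no sign that exclusion after dosing was a deliberate design decision.

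The consequence is limited. If a site acts on the literal instruction, up to 252 or 168 days of safety follow-up may be lost for that volunteer, and up to a nominal 28 days of events before the visit may go unrecorded. This assumes that exclusion from the trial is taken to end contact, which the protocol neither states nor rules out. The event should be rare; the range of 0.07 to 0.35 expected pregnancies rests wholly on the assumed number of women and pregnancy rate. The point still merits correction because safety is the primary objective, the groups are small and the missing information could not be recovered.

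**What to change.** Reconcile section 4.2 (lead-in and item 16), section 4.4, section 4.6 (opening and item 7), the Day 84 and Day 168 lists in section 6.4, and section 6.4.1, so that one consequence is stated for a positive pregnancy test after at least one dose. Add a cross-reference from both visit lists to the section that governs. State which adverse event, serious adverse event and pregnancy-outcome data are then collected, on what schedule, and that these data and those already held enter the safety analysis. Make clear whether events since the previous visit are recorded at the visit where the test is positive.

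Which clinical rule should apply is for the sponsor and investigators to decide.

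The cost is a few sentences in an amendment. If continued follow-up is the chosen consequence, the modified visit schedule already exists in 6.4.1 and Appendix 1. Sample size and analysis methods are unaffected.
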